### Researching complexity

Social accountability as a complex process poses challenges in neatly linking intervention to the outcomes. The MRC guidance on evaluating complex interventions calls for a combined evaluation of outcomes alongside process
^25^. It is necessarily to know whether the intervention ‘worked’ but also how they were implemented, their causal mechanisms and how effects differed from one context to another. The MRC recommends that such evaluations: identify how the intervention works in everyday practice; explain the discrepancies between expected and observed outcomes; understand a wide range of effects; and determine how the intervention effects vary among recipients, in different sites, over time
^25^. The CaPSAI Project study design takes into account these noted complexities (
Table 4).

**Table 4. T4:** Accounting for complexity in the Community and Provider driven Social Accountability Intervention (CaPSAI) study design.

Dimension of complexity (MRC)	CaPSAI dimension	MRC recommended design features	CaPSAI study design features
A large number of interactions between components within the intervention ^24^.	CaPSAI intervention requires separate and joint activities with community organizations, health providers, and duty bearers to produce an effective space for collective action and change.	A theoretical understanding of how the intervention causes change ^24^.	CaPSAI developed a theory of change ( Figure 1)
A number of behaviors required by those delivering or receiving the intervention ^24^.	Behavior change in varying degrees on the part of community members, health providers, and duty bearers is required for effects to take hold.	A process evaluation design to study the implementation process to address ‘how’ the intervention worked in practice and better understand the ‘active ingredients’ ^24, 25^.	Process evaluation is a main component of the study design
A number of groups or organizational levels targeted by the intervention ^24^.	CaPSAI intervention targets community members, health care providers and duty-bearers at the community and facility level.	A larger sample size and cluster rather than individual level designs ^24^.	Evaluation and sampling at both the community (individual) and health facility level (cluster).
Numerous and variable outcomes ^24^.	The primary outcomes include an increase in contraceptive uptake and indicators of contraceptive use alongside intermediary outcomes such as increases in social capital, collective efficacy, and empowerment.	Use of a range and mix of measures and methods to capture complexity and unintended consequences ^24, 25^.	A range of methods and instruments aim to capture the primary and intermediary outcomes as well as the implementation process itself.
A degree of flexibility or tailoring of the intervention is permitted ^24^.	Implementation should maintain conceptual fidelity to the eight standard steps but allows for local adaptation to produce the effects.	Fidelity should be considered ‘functionally rather than compositionally ^32^ to allow interventions to be responsive to context while still being meaningfully evaluated ^24, 25, 37^.	The process evaluation and combination of research instruments has been designed to capture functional fidelity in the implementation

MRC, Medical Research Council.

### Ethics issues

The intervention can be described as being an uncontained and unpredictable social process and some risks may arise, such as the occurrence of social harms from participating in the intervention activities as well as identification of “unusual occurrences” or “patterns of problems” during meetings. The implementation team will aim to minimize possible incidents of social harm by doing a thorough introduction of the project at various levels of administration (regional, district, ward or area).

Although the study is expected to be of minimal risk as no biological samples are collected, no drugs are provided, and no medical procedures are conducted, patients and health workers being interviewed may find some questions sensitive or embarrassing. While narrating their life stories they may become emotional as they remember important events. Interviewers will possess basic counseling skills to deal with such risks and will be able to refer HIV-positive patients to counselors within the local HIV care programme if required. There are no direct benefits to the respondents from participating in this study.

### Study limitations

There are limitations to the study design.

There is a risk of under-estimation bias if, despite intervention coverage in the study facility/catchment area, some women choose to go to one facility over another facility in the (same catchment area).

The cohort study may experience limitations due to loss to follow up, the large numbers needed for the sample and willingness to participate. One of the eligibility criteria will be willingness/anticipation of not moving outside the study area/district during the period of study. The check-up interviews at six months will also help address loss to follow-up and recall bias.

We anticipate that the research findings and conclusions from this study can be taken from the sample population to the population at large. The study is designed to capture the statistical probability from the quantitative studies/reliability of findings.

The measures used for the social accountability cross-sectional surveys have been adapted from related work; adaptations made to these items and response options may change the psychometric properties of the original measures
^47^. Attributing changes to the intervention directly poses a challenge. Respondent bias may pose a challenge as some measures discuss sensitive material.

Due to the lack of feasibility and budget to conduct intensive process evaluation data collection across all eight intervention sites, it was decided to do an in-depth focus on four implementation sites where NONs and IDIs will be conducted during key intervention activities. This allows for a very thorough understanding of implementation in four sites but compromises an overall view of the implementation by not collecting as much data in the other four intervention sites. However, documentation regarding intervention activities in all intervention sites, such as plans and reports created by the implementing CSOs, are analyzed to evaluate the dose, reach and fidelity of the implementation of the intervention across all sites.

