### Study objectives

As complex interventions, social accountability interventions have several interacting components where it is difficult to identify ‘the active ingredients’ producing effects, and a range of outcomes is possible
^24^. The Medical Research Council’s (MRC) guidance on evaluating complex interventions recommends evaluating outcomes alongside process
^25^. To inform policy and practice, we need to know whether interventions ‘worked’ or not, but also how they were implemented, their causal mechanisms and how effects differed from one context to another.

The CaPSAI Project examines both the impact and processes of a social accountability intervention in the context of FP/C programming. Specifically, it aims to measure the effect of the intervention on contraceptive uptake and use. It also aims to understand the mechanisms and contextual factors that influence and generate these effects.

Two objectives were identified:

1. To develop more responsive quantitative measures for social accountability as well as show the relationship between social accountability and uptake of contraceptives and use and other FP/C behaviors;2. To describe and examine how social accountability interventions are implemented and operationalized with a focus on understanding behaviors, decision-making processes, and the barriers and facilitators of change, with a view to generalizability.

To capture changes in contraceptive uptake and use, two designs are used:

i. 
*Contraceptive uptake*. A quasi-experimental pre-test post-test study, using a facility audit in both intervention and control facilities to determine the actual number of new users of contraception amongst women 15–49 in study catchment areas.ii. 
*Contraceptive use*. A cohort of women who are new users of contraception, using standardized interview questions across both intervention and control facilities are tracked to measure changes in behaviors around contraceptive.

To measure the effects of the social accountability intervention, two additional designs were also used:

iii. 
*Social accountability outcomes*. An evaluation of the intermediary outcomes related to the social accountability intervention, using a questionnaire of psychometric scales among health care providers and service users in the intervention facilities only. We also assess the feasibility, acceptability, and validity of the instrument.iv. 

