**Setting**	Intervention and control facilities	Intervention and control facilities	Intervention facilities	Intervention facilities N.B. The context mapping activity will be undertaken in both intervention and control sites (three interviews per district).
**Timing** *(N.B. Month 1–4* *was for preparing* *the study)*	Baseline: Month 5 Interim: Month 17 End-line: Month 29	Intake: Month 10–12 Check-up: Month 16–18 Follow up: Month 22–24	Pre-test: Month 5 Post-test: Month 17	8–12 data points tied to key events in the intervention facilities between Month 6 and Month 18. Eight events at four intervention facilities per country.
**Data sources**	Facility audit of FP/C facilities	Prospective cohort follow-up of new users	Cross sectional survey using a questionnaire of psychometric scales with women accessing FP/C and health care providers in intervention sites	Context mapping (three per district for both the intervention and control sites) In-depth interviews (three per observation) Observations (8–12 per process evaluation site) Document review

i. 
*Capturing changes in contraceptive uptake:* A quasi-experimental study utilizing an interrupted time series design with a control group (ITS-CG) is conducted to determine the actual number of new users of contraception amongst women 15–49 years old in eight intervention and eight control facilities per country. New users are defined as: never used an FP/C method (new acceptors); are switching from a traditional to a modern FP/C method (additional users); or are re-starting an FP/C method after a period of not using it for at least six months (additional users). The facility is the sampling unit.Contraceptive uptake in both the intervention and control arms is measured by comparing the level changes and trends over time during the study period. The numerator of the rate is measured using the facility audits provided by the intervention and control facilities, while the denominator of the rate, measured at the community level, is the number of women of reproductive age in the catchment area for the facility. The facility catchment area definitions used are those provided by Ghana Health Service in Ghana and the Ministry of Health in Tanzania. The catchment area study population size is collected from official statistics calculated on a yearly basis and, based on trend analysis, is expected to remain roughly constant throughout the study duration.ii. 

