*Contraceptive uptake:* For sample size calculations, it is assumed that, at pre-intervention, the mean number of new users per facility per month would be similar in both the intervention and control arms. It is further assumed that in the control arm, the pre-test and post-test mean number of new users per facility per month, per arm will remain the same. Study sample size and power were estimated in two ways: with the facility as the unit of measurement for Poisson regression, and with the monthly data points as the unit of measurement for time series regression. With the facility as the unit of sampling and of analysis, and assuming two-time points of interest, at pre-test (or baseline) and at post-test, different sample size estimates were computed using a two-sided t-test with Type I error at 5% level, statistical power at 80%, and assuming equal variance. These various sample size estimates are provided assuming a constant denominator (included as an offset in the Poisson model) and a pooled variance for mean number of new users at pre-intervention in both arms of between 100 and 200 new users per facility, per month, and a difference in uptake per facility per month, at post-intervention of between 60 and 200 new users. Approximately, five to eight facilities are needed per intervention or control group to detect an approximately two-fold increase in the rate of new users with 80% power and allowing for a 5% Type I error. The monthly data points were used as the unit of analysis and, based on effect size and time periods, the simulation-based power calculation provided by Zhang
*et al.*, 2011
^39^ was used. Assuming an effect size of 2.0 (derived from 100 new users in control group and 200 new users in intervention group and a pooled standard deviation of 50) and an autocorrelation of up to 0.3, a total of 12 data points – the equivalent to six monthly pre-intervention data points and six monthly post-intervention data points – would be needed to achieve 80% power at p=0.05 statistical significance level
^39^.ii. 

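### Facility choice is described only as a source of under-estimation, although an audit-count numerator over a roughly constant catchment denominator can also over-estimate uptake

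*Protocol article*

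**What the plan says.** Under Study objectives, the uptake component is meant to determine "the actual number of new users of contraception amongst women 15–49 in study catchment areas". The target is therefore a population, the women of the catchment areas.

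The measurement is set out in the Study design section, item i (contraceptive uptake). "The numerator of the rate is measured using the facility audits provided by the intervention and control facilities". The denominator, "measured at the community level, is the number of women of reproductive age in the catchment area for the facility". Its size comes from yearly official statistics and "is expected to remain roughly constant throughout the study duration". The Sample size section, item i, likewise works "assuming a constant denominator (included as an offset in the Poisson model". The Data analysis section then fits a segmented Poisson GEE model to rates per 10,000 women-months.

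On facility choice, Study limitations says: "There is a risk of under-estimation bias if, despite intervention coverage in the study facility/catchment area, some women choose to go to one facility". The alternative it has in mind lies within the same catchment. No other direction of bias from facility choice is mentioned in the article. The same section expects the findings to carry over to the wider population.

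**The concern.** Numerator and denominator describe different things. The numerator counts events at a building. The denominator counts women in an area and hardly moves. Any change in where women start contraception alters the numerator alone.

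Women leaving a study facility lower its rate, and this is the case the limitation covers. Women arriving raise it. Arrival at intervention facilities is what the protocol's own theory of change makes plausible, because it expects better service quality, counselling, interpersonal care, staffing and stock management there. A woman about to start a method who would have used a neighbouring facility may choose the improved one. She is then a new user at the study facility, but she adds nothing to uptake among catchment women.

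The control arm does not remove this. The shift coincides with the intervention in time and place, so the segmented model would read it as a change in level or trend. What is at stake is whether a positive estimate can be read as more uptake in the catchment or only as more new users at the study facilities.

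**Working it through.** **The plan's own figures.** The documents give no diversion share, so there is no stated bias figure to reproduce. The Sample size section gives a baseline of 100 new users, a target of 200 and a standard deviation of 50. The effect size (200 − 100)/50 = 2.0 and the two-fold ratio 200/100 = 2 both reproduce. These figures set the scale; they do not bear on the direction of bias.

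**Set-up.** Let B = 100 new users per facility per month before the intervention, with a constant denominator. Let R be the true rate ratio, i the share of B newly diverted in, and o the share newly diverted out. With control facilities unchanged:

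apparent rate ratio = (B·R + B·i − B·o)/B = R + i − o.

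The sign of the bias is the sign of i − o. The article names only the o term.

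**No true effect (R = 1); shares are assumptions.**

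| Share moved | Inflow from non-study facilities, 1 + i | Outflow, 1 − o |
|---|---|---|
| 5% | 1.05 | 0.95 |
| 10% | 1.10 | 0.90 |
| 20% | 1.20 | 0.80 |
| 30% | 1.30 | 0.70 |

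**Inflow from control facilities.** If the diverted women came from control facilities, the control rate would fall as well, and the ratio would be (1 + f)/(1 − f): 110/90 = 1.22 at 10% and 120/80 = 1.50 at 20%. This case depends on the geography of the arms (see the objection).

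**Could diversion alone give the two-fold effect?** From non-study facilities, 1 + i = 2 needs i = 100%. From control facilities, (1 + f)/(1 − f) = 2 gives f = 1/3, about 33%.

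**Could smaller shifts mislead a test?** As an illustration only, take a two-sided facility-level t-test at 5% with 8 facilities per arm and a standard deviation of 50. A pure diversion shift of 10 new users raises the rejection rate to about 6.6%, and a shift of 20 to about 11.6%. This is not the planned GEE model, and using 50 as the between-facility standard deviation is an assumption.

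**The case against.** The best defence is that the limitation is correct as scoped. A woman reached by the intervention who starts at another facility in the same catchment is missed, and that is under-estimation. The article does not say that this is the only bias. The Study setting section also states that outcomes are measured at facility level. This all stands, and it makes the point one of incompleteness. It does not answer the inflow case, and the stated target remains women in the catchment areas.

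Several stronger readings are tempting but not supported:

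- *The protocol treats its estimate as conservative.* A reader might infer this from the one-sided wording, but the article never calls the estimate conservative or a lower bound.
- *Every new user is counted wherever she lives.* The article says only that the numerator comes from facility audits. It describes no restriction by residence, but the audit form and registers are not shown. The point does not need this reading, since a catchment resident diverted from a neighbouring facility has the same effect.
- *The 1.22–1.50 range is the likely size.* That needs women to move from control to intervention facilities. The description of context mapping refers to intervention districts and control districts, which suggests, without proving, that the arms lie apart. Diversion would then mean travel between districts.
- *Diversion could produce the whole planned effect.* New users are never-users, women moving from a traditional to a modern method, and women restarting after at least six months without use. A continuing modern-method user who only changes facility is not counted, so the pool that can be diverted is limited.

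**Conclusion.** The point holds as an incomplete statement of bias for the uptake outcome. Under the protocol's own definition of the rate, facility choice can bias the estimate in either direction, and the control group does not protect against the upward one. With no true effect and an assumed inflow of 10–20% of baseline new users from non-study facilities, the apparent rate ratio is 1.10–1.20. Diversion from control facilities would give more, but is less likely if the arms lie in different districts. Diversion alone is unlikely to mimic a two-fold increase. The result rests on a constant denominator, unchanged control facilities in the main case, and a diversion share that the documents do not give. The true size is unknown. What changes is the conclusion the trial can draw: as described, the uptake measure supports a statement about the study facilities, not one about catchment women or the wider population.

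**What to change.** 1. Restate the limitation as possible bias in either direction: outflow lowers the estimate, and inflow to improved facilities raises it.
2. Word the uptake conclusion as new users at the study facilities, not as uptake among catchment women or the population beyond them.
3. Where routine monthly new-user counts can be had for neighbouring non-study facilities, compare their trend before and after the intervention. A fall there that coincides with a rise at the intervention facility would point to displacement. The Study setting section reports data gathered on at least 20 facilities, from which 16 were chosen in each country, so some non-study data (20 − 16 = at least 4 facilities) have been obtainable. Whether these are near neighbours, or hold monthly counts, is not stated.

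Two other checks should not be relied on. A table of residence among cohort women has no pre-intervention comparison, because intake is in Months 10–12, after step 6. A model restricted to catchment residents would still miss displacement between facilities inside the catchment, which is the situation the limitation describes.

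The cost is a narrower headline claim, some rewording and one small extra analysis. If no neighbouring counts exist, items 1 and 2 still apply and need no new data.

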## Conclusions

The completion of the study aims to provide researchers and implementers with the means to better measure and understand the mechanisms and contextual factors that influence social accountability processes in reproductive health, adding important findings to the evidence base. The study is expected to systematically assess social accountability processes, provide evidence of their effectiveness in improving FP/C services and demonstrate a relationship between the social accountability intervention and changes in contraceptive uptake and use. Though the findings may be context-specific, we anticipate this study will make a valuable and helpful contribution to the field with application to the development of FP/C programming in settings with significant unmet need.

An implementation manual for integrating social accountability processes in family planning service provision based on a set of effective practices will be developed and disseminated. At the end of the project, psychometric scales measuring social accountability intermediate outcomes in FP/C will be validated, ensuring more responsive quantitative measures for social accountability. The implementation and evaluation of the CaPSAI intervention are also expected to contribute to the existing evidence of conducting evaluations of complex interventions and inform reporting standards that enable a clear description of the interactions between research and implementation components and how these influence study results.

## Data availability

### Underlying data

No underlying data are associated with this article.

### Extended data

Figshare: CaPSAI Project - Extended Data.
https://doi.org/10.6084/m9.figshare.11743206
^42^

This project contains the following extended data:

- CaPSAI Informed Consent Forms-GH.pdf (sample consent forms and participant information sheets)- CaPSAI_FAU.pdf (facility audit questionnaire)- CaPSAI_ITS_CUI_FUI.pdf (intake, mid-term check-up and follow-up interview study instruments)- CaPSAI_XSU_XPV.pdf (social accountability questionnaire)- ContextMapping_ProcessExaluation.pdf (process evaluation NON and IDI instruments)

Data are available under the terms of the
Creative Commons Attribution 4.0 International license (CC-BY 4.0).
